### Inclusion and Exclusion Criteria and the Recruitment Process

The inclusion and exclusion criteria are outlined in Textbox 1. The dropout criterion is withdrawing consent during the study period.

In the Greek pilot where randomization of patient cohorts would occur, a simple coin toss algorithm will be used, implemented by Excel’s (Microsoft Corp) RANDBETWEEN function. This will allocate patients between the VP education cohort and the control (normal clinical information) cohort. In the Ukraine pilot, a sampling of convenience will allocate most of the participants to the VP cohorts and fewer to the control (normal clinical information) cohort. In the Kazakhstan pilot, all accepted patients will be allocated to the VP intervention cohort. While this decision by the medical team of this center makes impossible the conduct of a distinct local evaluation of impact, we chose to include the sample in the multicentric data processing part of the study. It should be noted that evaluation results will be extracted on a per-site basis only in the Greece and Ukraine arms of the study. In the multisite comparison, the whole sample of intervention patients (including the totality of the Kazakh cohort) will be compared to the totality of the sample of control patients from Greece and Ukraine cohorts.

Patients who meet the requirements for that study will be informed about the study and will be asked if they would like to participate in it. They will then sign the consent form to take part in the study. Patients who may withdraw their consent during the study will be excluded from the analysis.

Study inclusion and exclusion criteria.

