### Intervention Cohorts

The full pilot arm of the study will be conducted multinationally in Greece, Ukraine, and Kazakhstan (Figure 1). In Greece, a pool of 700 patients will be reached by phone, and they will participate in the trial from their home. From among the patients contacted remotely, and from those who respond, those who would be eligible will be asked to complete the intervention. From among the patients who choose to complete the quiz, half of them will be randomly allocated to the control (normal clinical information) cohort, while the other half will be informed with the help of VP vignettes. In Ukraine, 160 patients will be reached and will be divided into the control and intervention groups. Finally, at the Kazakhstan center, 190 patients will be contacted.

Given that all recruitment and adherence criteria are followed, sufficient sample sizes for control and intervention groups will be ensured so as to use the Welch *t* test for analysis, which is robust to large sample size inequalities, in order to not exclude any useful data from the generalized multicenter VP cohort.

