### Evaluation Design

#### Evaluation Instruments

For educational efficacy, a multiple-choice questionnaire (MCQ) for knowledge retention will be used (Textbox 2). The choice of questions was based on the European Society of Cardiology’s *Guidelines for Management of Atrial Fibrillation* [29]. This instrument will be translated for all participating centers in Greece, Ukraine, and Kazakhstan. The translation and evaluation of the translation will be performed by teams of bilingual experts. The instrument in its original version will be provided to bilingual persons in alternating language order and will be assessed accordingly. Scoring each questionnaire follows a simple process of allocating a numerical score equal to the number of choices in the MCQ to weigh each response for randomly selecting the correct question. For example, a question that has 4 possible responses in the MCQ will be scored 4 points if answered correctly, while a question that has 5 possible answers will be scored with 5 points if correctly answered.

Questionnaire for knowledge retention on atrial fibrillation (the asterisk indicates the correct answer).

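### Kazakhstan gives no local efficacy contrast and mixes country with VP effect in the pooled comparison; if the centre accepts a deferred VP, randomising the order would avoid both

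*Protocol article*

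**What the plan says.** Study Design describes a two-arm, parallel-group pseudorandomised trial. Its research question is comparative: VP scenarios against conventional patient education. Efficacy and acceptance are the primary outcomes.

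Inclusion and Exclusion Criteria and the Recruitment Process then sets a different allocation rule for each country. Greece uses a coin-toss algorithm. Ukraine allocates by convenience, mostly to the VP. For the third site, "In the Kazakhstan pilot, all accepted patients will be allocated to the VP intervention cohort". The article accepts what follows from this ("While this decision by the medical team of this center makes impossible the conduct of a distinct local evaluation of impact") and continues: "we chose to include the sample in the multicentric data processing part of the study".

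Two further sentences in that section fix how the data are used. First, "evaluation results will be extracted on a per-site basis only in the Greece and Ukraine arms of the study". Second, in the multisite comparison all intervention patients, including the whole Kazakh cohort, are "compared to the totality of the sample of control patients from Greece and Ukraine cohorts".

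Intervention Cohorts gives the numbers contacted: 700 in Greece, 160 in Ukraine, and "at the Kazakhstan center, 190 patients will be contacted". On the outcome measure, Evaluation Instruments says: "This instrument will be translated for all participating centers in Greece, Ukraine, and Kazakhstan". The control condition is information dictated by the research doctors.

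**The concern.** With no Kazakh comparator, the Kazakh quiz scores cannot answer the research question locally. The chosen scenario is to be localised for each centre, so the Kazakh version is never tested against normal information in the same language and care setting.

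The same patients then sit on one side only of the pooled comparison. Any difference between Kazakhstan and the other two countries in prior knowledge, translation of the quiz or usual care goes straight into the pooled VP-minus-control difference. The Welch test handles unequal variances and group sizes. It does not remove a difference in country mix between the groups.

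A policy that everyone receives the VP excludes a group that never receives it. It does not by itself exclude randomising whether the efficacy quiz is taken before or after the VP. The article neither considers that option nor says why the VP would have to come first.

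**Working it through.** **No figure to reproduce.** The article states no alpha, power, effect size or SD. I assume two-sided 5%, 80% power, equal halves, and effects in SD units of the quiz score. Participation is not given, so it is shown as a range. The 190 are contacts and therefore an upper bound.

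**What the plan yields.** Kazakhstan is 190 of 700 + 160 + 190 = 1,050 contacts, or 18%. It has no local controls, so no local contrast can be estimated.

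**Country effect in the pooled comparison.** Assume 60% to 90% of the 160 Ukrainian patients receive the VP (the article says only that most do).
- Full participation everywhere: the VP group is 350 + 96 + 190 = 636 at the 60% share and 350 + 144 + 190 = 684 at 90%. The Kazakh share of the VP group is 190/636 = 30% to 190/684 = 28%. Equal lower participation at all three sites leaves these shares unchanged.
- Greek participation 30% (105 per arm), with everyone contacted elsewhere taking part: the VP group is 391 to 439, and the Kazakh share is 49% to 43%.
- Suppose Kazakh scores differ from the other two countries by 0.3 SD for reasons unrelated to the VP (an assumption for illustration). The pooled difference shifts by 0.3 × share. That is 0.08 to 0.09 SD in the first case and 0.13 to 0.15 SD in the second, with no VP effect at all.

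**What randomised order would yield in Kazakhstan.** Detectable difference = (1.960 + 0.842) × √(2/n), where n is the number per order.

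| Participation | n per order | Detectable (SD) | Power for 0.5 SD |
|---|---|---|---|
| 100% | 95 | 0.41 | 93% |
| 75% | 71 | 0.47 | 85% |
| 50% | 47 | 0.58 | 68% |
| 30% | 28 | 0.75 | 46% |

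**What it adds to Greece.** With 1:1 allocation at each site, a common effect and equal variances, a site-stratified contrast has the precision of the summed numbers per arm. Power for 0.3 SD is approximately Φ(0.3 × √(n/2) − 1.960).
- Greece alone at 30%: n = 105, power about 58%.
- Plus Kazakhstan at 30%: n = 105 + 28 = 133; 0.3 × √66.5 = 2.446; Φ(0.486) gives about 69%.
- Plus Kazakhstan at 75%: n = 105 + 71 = 176; 0.3 × √88 = 2.814; Φ(0.854) gives about 80%.
- Greece alone at 50%: n = 175; 0.3 × √87.5 = 2.806; Φ(0.846) gives about 80% without Kazakhstan.

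The rise from 58% to 80% therefore needs much higher participation in Kazakhstan than in Greece.

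**The case against.** A reader might infer that the protocol's statement of impossibility is itself an error. The document does not support that. In a parallel-group design with every local patient allocated to the VP cohort, there is no local comparator, and the article says so openly and claims no Kazakh site result. Under randomised order, half the Kazakh patients would act as controls for the quiz. That changes the centre's allocation and is not merely a rereading of it.

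Four other objections carry weight.
- The centre's reason is not stated. If it requires immediate VP access, or cannot deliver the dictated information, a deferred VP fails as well.
- Quiz timing is not fixed. Evaluation Instruments calls the quiz a test of knowledge retention, while Study Design and Intervention Cohorts describe allocation among patients who complete the quiz. If the quiz is a delayed test, the second group waits for the VP throughout that interval.
- Acceptance is a primary outcome. Patients who rate the VP after hearing the normal information and sitting the quiz may rate it differently from VP patients elsewhere.
- The combined power figures assume one common effect across separately localised scenarios.

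These points limit how firmly the change can be recommended. They do not remove the mixing of country and VP effect in the pooled comparison. Disclosing that no local result is possible does not correct that comparison.

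**Conclusion.** The point holds in a conditional form. As planned, Kazakhstan contributes no local efficacy contrast, and its patients mix a country difference into the pooled VP effect. At equal participation across sites they are about 28% to 30% of the pooled VP group, given a 60% to 90% VP share in Ukraine. This is avoidable only if the centre's requirement is that all patients receive the VP, and not that they receive it before the quiz. That must be confirmed with the centre.

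The main gain is an unconfounded Kazakh estimate, with a detectable difference from 0.41 SD (all 190 take part) to 0.75 SD (30% take part). The gain in overall randomised power depends on participation. From 58% with Greece alone at 30%, it rises to about 69% if Kazakhstan also reaches 30%, and to 80% if it reaches 75%. If Greece reaches 50%, it already has about 80% alone. All these figures rest on the assumed two-sided 5% level and, for the overall power, a 0.3 SD effect.

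**What to change.** First ask the Kazakh centre why all its patients are allocated to the VP, and whether a VP given after the quiz is acceptable. If it is, make these changes together in Inclusion and Exclusion Criteria and the Recruitment Process:

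1. **Allocation.** Randomise accepted Kazakh patients by the Greek procedure to (a) VP, then quiz, or (b) normal dictated information, then quiz, then VP. State that in (b) the VP follows the quiz used for efficacy, and fix when that quiz is taken.
2. **Per-site results.** Add Kazakhstan to the sites with a local result, defined as the quiz difference (a) minus (b).
3. **Pooling.** Replace the pooling of all Kazakh patients as VP patients with a site-stratified contrast in which order (b) counts as control for the quiz. Changing the allocation alone would leave patients given normal information first counted on the VP side. The Ukrainian contrast stays non-randomised and should be labelled so.
4. **Acceptance.** Report it for all Kazakh patients by order, with order (a) as the group comparable to VP patients elsewhere.

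The cost is protocol wording, translation of the dictated text and a randomisation list for the site. No extra patients or instruments are needed. The downsides are a deferred VP for half the Kazakh patients (longer if the quiz is a delayed retention test) and a possible order effect on acceptance.

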## Methods

### Study Design

This is a 2-arm, parallel-group pseudorandomized controlled trial that will be performed at 3 sites—Greece, Ukraine, and Kazakhstan—and will include the evaluation of the educational VP interventions. This will be conducted in 2 axes that correspond to the primary outcomes of the study. The first axis aims to determine the efficacy of the educational VP interventions, while the other will involve assessing the acceptance and opinions of the participants about the VP modality for education and information purposes. Correspondingly, the primary outcomes of the study include the efficacy and the acceptance of the VP interventions, and the secondary outcomes include the opinions of the participants about the VP modality for education and information purposes. The aims of the study are summarized in the following research question: are patients with AF better educated about their post–acute phase lifestyle changes and needs by using mobile virtual scenarios compared to conventional patient education methods?

Α prepilot arm of the study will be initially conducted in Greece and will consist of hospitalized patients due to AF episodes, all of which should complete a short quiz. From among the patients who complete the quiz, half of the patients will be randomly allocated to the control (normal clinical information) cohort, while the other half will be informed with the help of VP vignettes.

After the prepilot arm, the pseudorandomized controlled trial will be conducted multicentrically. The same process, as in the prepilot arm, will be followed for recruiting the core sample, exploring the efficacy and impact of VPs in educating patients with AF. Since this trial will have been conducted during the COVID-19 pandemic, all national and international health and safety protocols will be followed.

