## Results

The trials will start in 2024 and are expected to end later that year or in early 2025 or when the needed sample size is achieved. The initial results are expected by March 2024.

To assess the results from the prepilot evaluation questionnaires, the Welch *t* test will be conducted. Of note, we decided to conduct the Welch *t* test because some of our sample sizes will be heavily unequal between intervention and control groups. The standard Student *t* test is robust to inhomogeneity of variance when sample sizes between cohorts are the same; however, this is not true for largely differing cohort sample sizes. The Welch *t* test does not assume homogeneity of variance and, hence, is robust to widely varying sample sizes [30,31].

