### Limitations

The study’s core limitation lies with the knowledge retention questionnaire. This is not a validated instrument. While we were aware of a formal validated instrument (the Jessa Atrial fibrillation Knowledge Questionnaire [40]), the knowledge spectrum that it covers is far wider than what our VP vignette may cover. Given that verbal and printed conventional information covers all relevant material, while our VP may cover specific critical topics related to AF, using a wide instrument such as the Jessa Atrial fibrillation Knowledge Questionnaire would run the risk to evaluate knowledge retention gaps that the VP vignette cannot cover. While a counterargument can be made that we are thus narrowing the evaluation scope to the strong points of our VP resource, the concise focus of the VP vignette is itself an argument for implementing it as a more effective educational tool in personalized and focused endeavors for patient empowerment. As a follow through too, we aim to address the second weakness of our study, which is the lack of a qualitative exploration about the acceptance of patients regarding the electronic medium of mobile devices and the modality of VPs in comparison to other existing modalities such as video demonstration or even gamified virtual environments.

Even given these limitations, however, this study can provide evidence for the comparatively better efficacy of the VP modality in mobile media for impactful and effective information for and empowerment of patients with AF. This study would be the first evidence-based step to initiate this process toward better informing and subsequent empowerment of patients with regard to the management of their disease.

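### Efficacy is evaluated in Greece, in Ukraine and in a multisite pool, but the protocol does not say which comparison answers the research question, and the pool it leans towards is not randomised

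*Protocol article*

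**What the plan says.** Protocol article, Study Design: there is one research question, whether VP scenarios educate patients with atrial fibrillation better than conventional methods. Also, "the primary outcomes of the study include the efficacy and the acceptance of the VP interventions". No site or sample is attached to efficacy.

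Inclusion and Exclusion Criteria and the Recruitment Process: Greece allocates by a random coin toss. Ukraine allocates by convenience, with most patients going to VP. Kazakhstan gives VP to everyone, and the text concedes that no local evaluation of impact is possible there. It then says that "evaluation results will be extracted on a per-site basis only in the Greece and Ukraine arms of the study". For the pooled analysis it says that "the whole sample of intervention patients (including the totality of the Kazakh cohort) will be compared to the totality of the sample"; the controls there are those recruited in Greece and Ukraine.

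Intervention Cohorts: in Greece "a pool of 700 patients will be reached by phone", and of those who complete the quiz "half of them will be randomly allocated to the control (normal clinical information) cohort". Ukraine approaches 160 patients and Kazakhstan 190. The Welch test is justified here by the wish to keep all data in the multicentre VP cohort.

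Results: a Welch test is also set for the prepilot, introduced with "To assess the results from the prepilot evaluation questionnaires".

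Limitations: "this study can provide evidence for the comparatively better efficacy of the VP modality in mobile media". This refers to the study, not to one of its comparisons.

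**The concern.** The three comparisons are not interchangeable. Only the Greek one is randomised. The Ukrainian one can be confounded by whatever guided the convenience allocation. The pool takes its VP patients from three countries and its controls from two, so a difference in score between countries enters the estimated effect.

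The comparisons can therefore disagree, and the protocol gives no rule for what the trial then concludes. If the Greek result is null and the pool is significant, the claim could rest on the weaker evidence. If any significant result may be put forward, the error rate of the study's conclusion also exceeds that of a single test.

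**Working it through.** The protocol states no alpha, power, SD or target sample size, so it has no figure of its own to reproduce.

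**Inputs from the protocol.** Numbers approached are 700 (Greece, split 1:1), 160 (Ukraine, mostly VP) and 190 (Kazakhstan, all VP).

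**Assumptions.** Two-sided 0.05 per test; equal SD; no country differences; Ukraine 60 to 90% VP; various response rates; any significant result may carry the claim.

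**Step 1: overlap of the tests.** In SD units, SE = √(1/n_VP + 1/n_control). Each site's patients are part of the pool, so the correlation of a site's test with the pooled test is SE_pool / SE_site. With full response and Ukraine 75% VP:

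| Comparison | VP | Control | SE | Correlation with pool |
|---|---|---|---|---|
| Greece | 350 | 350 | 0.0756 | 0.0639/0.0756 = 0.845 |
| Ukraine | 120 | 40 | 0.1826 | 0.0639/0.1826 = 0.350 |
| Pool | 350+120+190 = 660 | 350+40 = 390 | 0.0639 | 1 |

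**Step 2: false-positive chance with no true effect.** A trivariate normal with these correlations gives:
- at least one of three tests significant in favour of VP: 6.0%, against 2.5% for one test;
- at least one of three significant in either direction: 11.8%, against 5%.

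If an independent prepilot test also counted:
- in favour of VP: 1 − (1 − 0.060) × 0.975 = 8.3%;
- in either direction: 1 − (1 − 0.118) × 0.95 = 16.2%.

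Independent tests would give the ceilings for three: 1 − 0.975³ = 7.3% and 1 − 0.95³ = 14.3%.

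Simulation with Greece 100 to 700, Ukraine 80 to 160, Kazakhstan 95 to 190 and a prepilot of 50 gave 5.9 to 6.6% in favour of VP and 11.7 to 12.9% in either direction for three tests. For four tests it gave 8.2 to 8.7% and 16.1 to 16.9%. Over all runs, including those with full Welch tests, the rounded ranges are 6 to 7% and 11 to 14% for three, and 8 to 9% and 15 to 18% for four.

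**Step 3: power and disagreement at a true effect of 0.2 SD, full response.**
- Greece: 0.2/0.0756 = 2.65; power ≈ Φ(2.65 − 1.96) = 0.75 (0.76 in simulation).
- Pool: 0.2/0.0639 = 3.13; power ≈ Φ(3.13 − 1.96) = 0.88.
- With correlation 0.845, one is significant and the other is not in about 16% of trials. Over response rates of 30 to 100% the figure is about 15 to 22%. Mostly it is the pool that is significant alone.

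**Step 4: why the pool cannot simply be declared the answer.** Take 350/80/95 patients with Ukraine 75% VP. The VP arm is 175 + 60 + 95 = 330 and the control arm 175 + 20 = 195, so SE = 0.0903. If Kazakh patients score 0.2 SD higher for reasons unrelated to VP, the pooled difference is biased by 0.2 × 95/330 = 0.058 SD, or 0.64 SE. The chance of a false result favouring VP in the pool alone is then 1 − Φ(1.96 − 0.64) = 9.3%. The 0.2 SD shift is illustrative. This bias comes on top of the multiplicity figures, which assume no country differences.

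**The case against.** The strongest reply is that this is a condensed article and that alpha and multiplicity rules may stand in an analysis plan that is not shown. That holds for the rules: their absence is not the point. What remains is that the article itself defines the comparisons and attaches its primary efficacy question to none of them.

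A second reply is that the pool is evidently meant. The trial is presented as multicentre, Study Design treats the multicentre patients as the main sample, and the Welch justification concerns the multicentre cohort. These passages do lean towards the pool, but none says that it decides. If it does, the primary answer comes from a non-randomised contrast, which is a reason to make the choice openly.

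Third, per-site results are routine, and the sentence on them restricts reporting rather than declaring hypothesis tests. This is fair. The protocol nowhere says that any one significant result suffices, and its conclusion is hedged. The error rates are therefore conditional on that reading.

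Four stronger readings are tempting, and the documents do not support them:
- A reader might attach the 11 to 14%, or 15 to 18%, to a false claim that VP is better. Those figures count results in either direction; for a claim in favour of VP they are about double the right ones.
- A reader might count the prepilot as a fourth route to the claim. It precedes the trial proper, its size is not given, and no text lets it carry the conclusion.
- A reader might take disagreement among all three tests as the measure of the problem. The Ukrainian comparison is small and unequally split, so that mostly reflects low power. Greece against the pool is the relevant pair.
- A reader might think a confirmatory pooled test is safe once Greece is significant. Sequencing orders the tests; it does not remove confounding by country.

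**Conclusion.** The concern holds in this form: three evaluations of one efficacy question, of differing validity, with none named as deciding and a conclusion worded for the whole study. The firm part needs no assumption: when Greece and the pool disagree, the trial has no predefined answer, and the text leans towards the non-randomised one.

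The size is conditional on the assumptions listed in the working. Under them, the chance of a false result favouring VP rises from 2.5% to about 6 to 7%, or 8 to 9% if the prepilot also counted. At a true 0.2 SD, Greece and the pool disagree in about 15 to 22% of trials. The change should be made before data are analysed; it is a matter of interpretation and does not invalidate the Greek comparison.

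**What to change.** In Study Design and in the recruitment section, name one deciding efficacy contrast: VP against control on the multiple-choice questionnaire score in the randomised main Greek sample, excluding the prepilot. State its test level; two-sided 0.05 is assumed here. Label the Ukrainian, multisite and prepilot comparisons as supportive, reported with confidence intervals and without a confirmatory claim. Do not add a confirmatory pooled test in fixed sequence. Reword the efficacy conclusion in Limitations so that it rests on the Greek contrast.

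The cost is wording only, with no extra patients or data. The deciding test has about 2 to 16 percentage points less power than the pooled test over effects of 0.2 and 0.3 SD, for example 0.76 against 0.88 at 0.2 SD with full response. The pool's advantage is itself computed with no country differences. The deciding result would apply to Greece only, and a significant Ukrainian or pooled result could no longer carry the claim alone.

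### The multisite comparison pools an all-VP Kazakh cohort against Greek and Ukrainian controls, and the Welch t test does not remove the resulting country difference

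*Protocol article*

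**What the plan says.** The section on inclusion criteria and recruitment sets a different allocation rule at each site. In Greece, "a simple coin toss algorithm will be used". In Ukraine, "a sampling of convenience will allocate most of the participants to the VP cohorts and fewer to the control (normal clinical information) cohort". For the third site, "In the Kazakhstan pilot, all accepted patients will be allocated to the VP intervention cohort". The same section concedes that no local evaluation of impact is possible in Kazakhstan, and plans per-site results for Greece and Ukraine only. It then fixes the multisite contrast: "the whole sample of intervention patients (including the totality of the Kazakh cohort) will be compared to the totality of the sample" of control patients, who come from Greece and Ukraine.

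The section Intervention Cohorts ties the Welch t test to this pooled cohort, calling it "robust to large sample size inequalities, in order to not exclude any useful data from the generalized multicenter VP cohort". The Results section, speaking of the prepilot questionnaires, gives the reason for the choice: the test "does not assume homogeneity of variance and, hence, is robust to widely varying sample sizes". No site term, stratification or within-site combination is mentioned. The Limitations section discusses the unvalidated questionnaire and the missing qualitative work, but not the mixing of country with treatment.

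**The concern.** A two-sample test compares two arm means. Here the arms contain different proportions of each country, so the difference in means carries country differences as well as any VP effect. Welch's correction acts on the standard error and the degrees of freedom. It leaves the estimate unchanged, so robustness to unequal group sizes is no reason for including a cohort that has no controls.

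Kazakhstan holds no within-site information on VP versus control. Whatever it adds to the contrast is a comparison between countries. Country differences in score are plausible from the protocol itself: the quiz is translated for each centre and is not a validated instrument, and the scenario is adapted locally. Efficacy is a primary outcome. The multisite result could show an effect that does not exist or hide one that does, depending on the sign of the country gap.

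**Working it through.** **Inputs from the protocol (Intervention Cohorts).** "In Greece, a pool of 700 patients will be reached by phone", with half of those who complete the quiz randomised to each arm. "In Ukraine, 160 patients will be reached and will be divided into the control and intervention groups". In Kazakhstan 190 patients are contacted. These are numbers reached, not enrolled. The protocol gives no sample size, SD, alpha or effect size, so there is no figure of its own to reproduce.

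**Assumptions.** Everyone reached takes part; Ukraine is 75% VP; within-country SD is 1; the test is two-sided at 0.05; the score after the intervention is analysed; the VP has no true effect.

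**Arm composition.**

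| | VP | Control |
|---|---|---|
| Greece | 350 (53.0%) | 350 (89.7%) |
| Ukraine | 120 (18.2%) | 40 (10.3%) |
| Kazakhstan | 190 (28.8%) | 0 (0%) |
| Total | 660 | 390 |

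**Bias.** With no VP effect, the expected difference is the sum over countries of (share in VP − share in control) × country mean. Taking Greece as reference:

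bias = 0.288 × (Kazakh − Greek mean) + 0.079 × (Ukrainian − Greek mean)

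**False-positive rate.** Pooled SE = √(1/660 + 1/390) = 0.0639 SD. The rate is P(|Z + bias/SE| > 1.96).

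- Kazakh gap 0.3 SD: bias 0.288 × 0.3 = 0.086 SD; bias/SE = 1.35; about 27%.
- Kazakh gap 0.5 SD: bias 0.288 × 0.5 = 0.144 SD; bias/SE = 2.25; 62% with the SE held fixed. The country gap also widens the spread of the VP arm, and allowing for that gives about 60%.
- Gap of 0.3 SD in both Kazakhstan and Ukraine: bias 0.110 SD; about 40%.

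Simulating 4,000 trials with the Welch test gave 27.0%, 60.1% and 40.4% for these cases, and 5.2% with no country gap. A model with a site term rejected in 4% to 6% of trials in every case. A lower Kazakh mean gives the same bias in the opposite direction.

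**Sensitivity.** With Greek enrolment between 25% and 100% (the other sites complete) and a Ukrainian VP share between 60% and 90%:

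- The Kazakh coefficient runs from 0.28 to 0.51.
- The false-positive rate is 13% to 18% at a Kazakh gap of 0.2 SD, 23% to 35% at 0.3 SD, and 53% to 75% at 0.5 SD.
- The Ukrainian coefficient runs from about −0.17 to +0.20. With full enrolment and 60% VP it is 96/636 − 64/414 = −0.004.

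With 50% participation at all three sites the composition is unchanged and the SE is larger, so the rates at 0.3 and 0.5 SD fall to 16% and 36%.

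**What pooling gains.** Greece alone: SE = √(1/350 + 1/350) = 0.0756 SD. The precision of the Greek contrast is 1/(1/350 + 1/350) = 175 and of the Ukrainian contrast 1/(1/120 + 1/40) = 30, so the site-stratified SE = √(1/205) = 0.0698 SD. Against the pooled 0.0639 SD these are about 18% and 9% larger. In mean squared error, pooling loses its advantage over the stratified estimate once the Kazakh gap exceeds √(0.0698² − 0.0639²)/0.288 ≈ 0.10 SD.

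**The case against.** The best defence has several parts.

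- **Per-site results are already planned and the pooling is disclosed.** Both are true. The protocol does not rank the multisite contrast above the site results, so a reader who infers that the trial's leading result is invalid, or that no sound comparison exists, goes beyond the text. But the disclosure covers only the lack of a local Kazakh evaluation, and the site results do not repair the multisite one.
- **An unseen analysis plan may adjust for site.** A site-adjusted VP-versus-control contrast gives Kazakhstan no weight. That conflicts with the comparison the protocol fixes, so the protocol wording would still have to change.
- **The evidence for country gaps is limited.** The translation is checked by bilingual experts, and recruitment is said to follow the same process as the prepilot. Phone contact is described for Greece, while the other sites' mode is not given. This stands: gaps are plausible, but their size and direction are unknown.
- **A change score could cancel fixed country differences.** The quiz precedes allocation in the described Greek pathway. The protocol does not say that change is analysed, and differences in learning or selection between countries would remain. This limits the size claimed, not the point.
- **Ukraine should not share the blame equally.** This stands. Its contribution can be near zero or of either sign. Its own problem is convenience allocation within the site.

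Nor is a misleadingly narrow interval the main fault. The SEs of 0.064 and 0.070 SD differ little; what matters is bias.

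**Conclusion.** The point holds for the multisite efficacy comparison as the protocol fixes it. Kazakh patients appear only in the VP arm, the only named test has no site term, and the stated justification concerns variances and group sizes rather than country mix. Kazakhstan is the main source of the bias.

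The base-case figures (27% and about 60% false positives) are illustrations. They rest on the assumed enrolment, the assumed Ukrainian split, analysis of the score after the intervention, and country gaps that the protocol does not supply. They do not show that the result will be biased by that amount or in favour of the VP. The planned Greek and Ukrainian site results are free of between-country confounding, and only the Greek one is randomised.

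**What to change.** 1. State that the already planned Greek randomised comparison of the quiz score carries the efficacy conclusion.
2. Replace the pooled Welch test with a site-stratified (site fixed effect) estimate from Greece and Ukraine, labelled supportive. Say that stratification does not cure convenience allocation within Ukraine.
3. Take Kazakhstan out of the between-arm efficacy contrast. Report it as a single-arm cohort: scores, completion and acceptance, with before/after scores only if a baseline quiz is taken there.
4. Delete the statement that the Welch test justifies including the Kazakh sample, and name the confounding of country with treatment in the Limitations section.

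The cost is 190 fewer patients in the contrast, with an SE about 9% larger (stratified) or 18% larger (Greece only) in the base case. The wording change is small, but its consequence is not trivial: the confirmatory claim would rest on one country of three.
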